#### Effectiveness

The primary outcome work participation will be analyzed in three steps. Step 1. For every time point (that is, T0 - T8, see Fig. 2), we will present the number of sick leave days as an absolute number and as a percentage related to contract hours/month, in which the absolute number and percentages between a given time point and the preceding time point will be calculated using linear extrapolation, as recommended [36, 44, 55]. Step 2. We will calculate and present the cumulative total days of sick leave per month from the start of the intervention until the 12-month follow-up using an area under the curve for all measurement points, in which the number of sick leave days between a given time point and the preceding time point will be calculated using linear extrapolation. Step 3. Linear mixed models with multilevel analyses will be performed to assess non-inferiority between the two groups at the 12-month follow-up (that is, intervention period and 12-month follow-up) by means of 95 % confidence intervals (that is, the CI approach). To improve generalizability and comparability of this study with other studies, we will repeat step 3 at the following time intervals: I) discharge to 12-month follow-up; II) start of intervention to 6-month follow-up; III) discharge to 6-month follow-up. These additional analyses will contain no conclusions about non-inferiority and will be analyzed in the “classical” superiority manner.

A t-test or Mann–Whitney U test (in the case of no normal distribution) will be used to examine differences at discharge, at 6-month follow-up, and at 12-month follow-up (defined as the difference in outcome between baseline and last follow-up) in all secondary outcomes between the intervention groups. We will perform these analyses on superiority, thus without margins of noninferiority, as this is only relevant for the analysis of the primary outcome.

#### Cost-effectiveness

Various kinds of economic evaluations are recommended for the same study to inform all relevant stakeholders [25]. We will perform three types of cost analysis: cost-effectiveness analysis, cost-utility analysis, and cost-benefit analysis.

##### Cost-effectiveness analysis: societal perspective

The cost-effectiveness analysis (CEA) in this study will be evaluated from the societal perspective (that is, all costs related to the intervention will be taken into account irrespective of who pays for them). Costs consist of direct medical costs (that is, intervention costs, health care usage and travelling costs) and indirect costs (that is, productivity loss in paid work due to absenteeism and presenteeism). All costs will be summated for each individual patient. All summated costs will be indexed in euros for the reference year 2015. We will follow the friction cost method with a friction cost period of 160 days and an elasticity of 0.8 for the calculation of absenteeism costs [56], as recommended by the Dutch guideline for health economic evaluations [35] and described in detail elsewhere [34, 56]. To calculate the presenteeism costs, the costs of productivity losses will be multiplied by the number of workdays lost, with age and gender-specific productivity levels per paid employee indexed for the year 2015 [34, 35].

Both the incremental costs and incremental effects will be used to calculate the incremental cost-effectiveness ratio (ICER). The ICER will be calculated as (C1 − C0)/(E1 − E0), where C denotes the average per-participant costs and E denotes the effect on work participation in the 40-h and 100-h VR groups (subscripted 1 and 0). As absenteeism data will be used for the assessment of the effect ratio of the ICER, it will be excluded from the cost ratio part of the ICER. The ICER can be interpreted as the net costs (or savings) per extra unit of effect. In our study, the extra unit of effect equals a 1-day increase in work participation. To estimate uncertainty in the cost and effect data, nonparametric bootstraps will be used to simulate 5,000 ICERs [57]. To show statistical uncertainty on the results of cost-effectiveness, each simulated ICER will be plotted on a cost-effectiveness plane [58]. Although cost-effectiveness planes give a good impression of the uncertainty surrounding the ICER, they do not provide a summary measure of the joint uncertainty of costs and effects [25]. We will therefore perform cost-effectiveness acceptability curves (CEAC), which will provide insight into the probability that 40-h VR is cost-effective in comparison with 100-h VR [25].

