### Statistical methods

All statistical analyses will be performed at the patient level, with descriptive statistics being used to compare the baseline measurements of the two intervention groups. If necessary, analyses will be adjusted for baseline differences. All analysis will be performed according to the intension-to-treat principle and the per protocol principle [30, 54]. To claim non-inferiority, both intention-to-treat and per protocol analysis must show non-inferiority [54]. Missing data on costs and effects will be assessed using multiple imputation techniques [25]. The imputation technique will depend on the results (that is, missing completely at random, missing at random, or missing not at random).

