### Sample size

A sample size of 174 is calculated to be sufficient (with a one-sided 95 % CI, 80 % power, alpha of 0.025, standard deviation of 80 and a margin of non-inferiority of 30 days) to establish non-inferiority of 40-h VR. The sample size calculation allowed for 15 % loss to follow-up - 10 % expected from comparable studies [18, 59, 60] and 5 % expected due to the extension of the program in the 40-h VR group. An intraclass correlation coefficient (ICC) of 0.05 is accounted for by the use of four rehabilitation centers with two clusters (40-h and 100-h VR) at each center [61, 62]. Because of the difference in program hours between 40-h and 100-h VR, we expect 40-h VR to benefit by 8 extra working days available during the intervention period. We accounted for this in the power calculation by using minus 8 as the expected mean difference between 40-h and 100-h VR. In our power calculation, we assumed a normal distribution of the primary outcome work participation. If the data on the primary outcome does not follow a normal distribution, we will perform log transformations. As previously stated, we will allow 28 % as the margin of non-inferiority when the data is log transformed.

According to the number of patients expected to be referred to the four participating rehabilitation centers per year (approximately 350), and after accounting for two-thirds of non-participation in the study according to Lasagna Law [63], we expect an inclusion of 115 participants per year for this study. Hence, our inclusion period will cover approximately 18 months, and the data collection period will cover 2 years and 9 months.

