### Methodological considerations

The first methodological consideration of this study is that we were not able to fulfil the recommended steps for the composition of a margin of non-inferiority [30, 65]. This was because there is currently no historical data, such as meta-analysis, comparing the 100-h vocational rehabilitation with usual care. However, our non-inferiority margin is based on results from five randomized controlled trials evaluating multidisciplinary vocational rehabilitation compared with control interventions (that is, usual care, such as occupational physician, physical therapist, occupational therapist, *etcetera*) [15, 17–19, 24]. These studies found 43 days as the mean difference ((41.9 + 53.7 + 42 + 60.5 + 17.5)/5) in days on sick leave after one year follow-up in favor of multidisciplinary vocational rehabilitation. Consequently, we have decided that 30 is an acceptable margin of non-inferiority. One can argue that this limit is too wide, and that claiming non-inferiority could be achieved too simply, but for claiming non-inferiority, the upper bound of the one-sided 95 % confidence interval of the treatment effect difference (40-h VR – 100-h VR) must be 30 or less. Furthermore, when the margin of non-inferiority of 30 is reached after 12 months follow-up, this is in fact 13 days (43–30) better than if a patient had been referred to usual care (occupational physician, physical therapist, occupational therapist, *etcetera*). A mean saving of 10 sick days per year is considered the smallest effect that would be clinically worthwhile [66]. We therefore consider 30 as a reasonable margin of non-inferiority. The second methodological consideration of this study is the slight differences between the participating rehabilitation centers. For instance, each center has its own logistic restrictions, such as a restriction in intervention facilities (that is, equipment, building); and centers have evolved their own methods over the years. This may lead to interpretation issues in analyzing the blended results of the four centers. However, we solved this problem by multilevel analyses and by performing both interventions at each center, that is, by randomizing at the participant level. Although performing both interventions at the center level may introduce contamination, we consider that the advantages of randomization at the participant level outweigh the disadvantages of contamination.

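### Secondary outcomes are tested without a centre or cluster term although the protocol assumes clustering by centre and programme, and the economic bootstrap does not say how it handles that clustering

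*Protocol article*

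**What the plan says.** **Clustering is assumed.** The Sample size section states, for every one of the centres: "An intraclass correlation coefficient (ICC) of 0.05 is accounted for by the use of four rehabilitation centers with two clusters (40-h and 100-h VR) at". That makes 4 × 2 = 8 clusters, each belonging to one arm.

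**Clustering is said to be dealt with.** Methodological considerations, on differences between centres, says: "we solved this problem by multilevel analyses and by performing both interventions at each center".

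**Only the primary outcome is modelled that way.** Under Effectiveness, step 3 for the primary outcome, and its repeats over other time intervals, use linear mixed models with multilevel analysis. The levels are not listed. For all secondary outcomes the same section says: "A t-test or Mann–Whitney U test (in the case of no normal distribution) will be used to examine differences" at discharge, 6 months and 12 months. No centre or cluster term is mentioned.

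**The economic analysis is silent on it.** The cost-effectiveness section says "nonparametric bootstraps will be used to simulate 5,000 ICERs", and the cost-benefit section adds 95 % bootstrap intervals for the benefits and the net benefit (NB). Neither gives the resampling unit, the strata or a model inside the bootstrap. The general statement "All statistical analyses will be performed at the patient level" opens Statistical methods.

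**Allocation.** Patients are randomized individually in blocks of four, with a separate table for each centre (Randomization).

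**The concern.** A t-test or Mann–Whitney test takes its error variance from the spread between patients and treats them as independent. If patients in the same programme at the same centre resemble each other, as the Sample size section assumes, a chance difference between the 40-h and 100-h clusters looks like a programme effect, and the test rejects too often.

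Such resemblance is plausible here. Both programmes are delivered in groups, each centre sets the number of sessions in the 40-h arm, the screening team chooses 30 of its 40 hours, and centres have developed their own methods. The claim that multilevel analysis solves the centre problem therefore does not reach the secondary outcomes as the plan is written.

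The economic analysis has a related problem of consistency. The sick-leave difference appears in the primary analysis with multilevel uncertainty and again as the effect in the ICER. Unless the bootstrap handles centre and programme in the same way, one quantity may carry two different uncertainties within the trial.

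**Working it through.** **Inputs.** From the Sample size section: "A sample size of 174 is calculated to be sufficient", with "80 % power, alpha of 0.025, standard deviation of 80 and a margin of non-inferiority of 30 days"; an expected difference of −8 days; 15 % allowance for loss; ICC ρ = 0.05; eight clusters. Assumed because the article does not say: the same ICC for the secondary outcomes, a two-sided 5 % level, equal cluster sizes, normal outcomes.

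**The plan's own figure.** Patients per arm without clustering:

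(1.96 + 0.8416)² × 2 × 80² / (30 + 8)² = 69.6, so 70 per arm and 140 in total.

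- Loss only: 140 / 0.85 = 165, which falls short of 174.
- With an ICC allowance: 140 × 1.05 / 0.85 = 173, or 140 / 0.95 / 0.85 = 173.4, rounded up to 174.

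So 174 reproduces with an inflation of about 1.05 for the ICC.

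**Cluster size.** 174 × 0.85 = 148 evaluable gives 18.5 per cluster; all 174 give 21.75. I use m = 19 (152 patients) for illustration.

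**Error of a test that ignores clusters.** Let f be the share of the ICC common to both arms of a centre. Because each centre runs both arms in balance, that share cancels from the arm difference. With total variance set to 1 and n = 4m patients per arm:

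- True variance of the difference, in units of 2/n: A = mρ(1 − f) + (1 − ρ).
- Variance that the t-test expects, same units: B = (1 − ρ) + ρ(n − m)/(n − 1).
- V = A/B, and the error is 2 × [1 − Φ(1.96/√V)].

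For m = 19, B = 0.95 + 0.05 × 57/75 = 0.988.

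| Share common to both arms (f) | A | V | 1.96/√V | Error |
|---|---|---|---|---|
| 0 | 1.900 | 1.923 | 1.413 | 15.8 % |
| 0.5 | 1.425 | 1.442 | 1.632 | 10.3 % |
| 0.75 | 1.188 | 1.202 | 1.788 | 7.4 % |
| 1 | 0.950 | 0.962 | 1.999 | 4.6 % |

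At f = 0, A is the usual design effect, 1 + 18 × 0.05 = 1.90; used alone it gives 1.96/√1.90 = 1.42 and 15.5 %. From 148 to 174 evaluable patients, the formula gives 15.5 to 17.2 % at f = 0 and 10.1 to 11.1 % at f = 0.5. At f = 1 it stays at 4.6 %.

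**Simulation check** (4 centres × 2 programmes × 19 patients, no programme difference; 10,000 runs, but 4,000 for Mann–Whitney and 2,000 for the bootstrap):

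| f | t-test | Mann–Whitney | 95 % bootstrap of single patients | t-test on cluster means (6 df) | t-test paired by centre (3 df) |
|---|---|---|---|---|---|
| 0 | 16.0 % | 15.0 % | 16.1 % | 5.2 % | 5.1 % |
| 0.5 | 9.9 % | 10.0 % | 10.9 % | 3.2 % | 5.0 % |
| 1 | 4.6 % | 4.8 % | 5.8 % | 1.8 % | 5.0 % |

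A second simulation with the same layout (3,000 runs) gave t-test errors of 16.1, 11.3 and 4.6 % for the same three rows.

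The bootstrap column shows what would happen if single patients were resampled; the article does not say that they will be. The last column shows that a comparison within centres, using the variation of the programme difference between centres, holds 5 % whatever the split.

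**The case against.** The strongest counter-argument is the design itself. Randomization is individual and balanced within each centre, so anything a centre does to both its programmes cancels. The article describes heterogeneity mainly as belonging to centres (facilities, equipment, habits grown over years) and accepts contamination between programmes, which also suggests shared influence. If all of the ICC is of that kind, the simple tests are slightly conservative. This stands: 16 % is the upper end of a range, not the expected value.

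The 174 also contains an ICC inflation of only about 1.05. A design effect for eight independent clusters (1.83 to 2.04 for 17.5 to 21.75 per cluster) would have led to about 301 to 336 patients. The planners therefore did not work with a factor near 1.9. That does not show how they thought the ICC splits, and the sample size is a separate matter.

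Three stronger readings are tempting, and the documents do not support them.

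- **That the error is 16 % on the protocol's own assumption.** The article names eight clusters but does not say how the 0.05 divides, and it gives the ICC in the sample size paragraph for sick leave, not for secondary outcomes or costs.
- **That the economic bootstrap treats patients as independent.** The resampling unit is not stated, and a condensed article may leave that to the full plan. The patient-level statement does not settle it, since it also covers the multilevel primary analysis.
- **That the cost-effectiveness answer is therefore invalid.** The plane and the acceptability curve involve no 5 % test, so an error rate does not describe them.

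None of this answers the point about the secondary outcomes. There the article does fix the method, and the method omits the clustering that the article assumes.

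**Conclusion.** The point holds for the secondary outcomes. The stated tests do not match the stated clustering assumption or the claim that multilevel analysis deals with centre differences. The error at a nominal two-sided 5 % lies between about 5 % and about 16 %, with about 10 to 11 % if half of the ICC is shared by both arms of a centre. This rests on carrying the ICC of 0.05 over to these outcomes, on a two-sided 5 % level, and on roughly equal clusters of about 19.

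For the economic analyses the conclusion is narrower: the handling of centre and programme in the bootstrap should be written down and made consistent with the primary analysis. If single patients were resampled, the 95 % interval for NB would be exposed to the same range of error, given the same ICC for costs. For the plane and the acceptability curve the possible harm is understated uncertainty, which cannot be sized from the article. The primary non-inferiority analysis, which has a multilevel model, is not affected by this point.

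**What to change.** **Effectiveness section.** Analyse the secondary outcomes with the same multilevel model as the primary outcome. Name its levels: centre, and programme within centre if that variance is supported by a rule set in advance. Use small-sample degrees of freedom. Keep the t-test and Mann–Whitney test as a sensitivity analysis.

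**Cost-effectiveness and cost-benefit sections.** State the resampling unit and make the bootstrap respect centre and programme, for example by bootstrapping around the same multilevel model. The sick-leave difference then carries consistent uncertainty in the primary analysis, the ICER plane, the acceptability curve and the NB interval. A full joint parametric model of costs and effects is not required; it would add distributional assumptions for costs that the bootstrap avoids.

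**Cost.** Wording and some programming; no new patients or data. Intervals become somewhat wider and the secondary comparisons lose power. Where the programme-within-centre term is kept and the degrees of freedom fall to about 3, the t multiplier is 3.18, against about 1.98 with 150 degrees of freedom, so the loss can be considerable. Four centres estimate a cluster variance poorly, which is why the rule for keeping that term should be fixed beforehand and the simple tests reported alongside.

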##### Cost-utility analysis

A cost-utility analysis (CUA) will be conducted in which the incremental costs per QALY will be estimated and which will be presented on a cost-effectiveness plane and CEAC. Public policymakers may be interested in CUA because they can compare the results between several conditions and interventions [25].

##### Cost-benefit analysis: employer’s perspective

As employers reimburse the work participation coordination module in both the 40-h VR and 100-h VR, analysis from the employer’s perspective (that is, only the costs relevant to the employer will be considered, including intervention, absenteeism, and presenteeism costs) is useful. It is recommended to conduct cost-benefit analysis (CBA), in which both costs and consequences are measured in monetary units. In accordance with van Dongen et al. [25], we will perform a return on investment (ROI) analyses, in which three ROI metrics are calculated: (1) net benefits (NB), (2) benefit-cost ratio (BCR), and (3) ROI.

NB = benefits − costs

BCR = benefits/costs

ROI = (benefits − costs)/costs [*100]

Costs will be defined as intervention costs. Benefits will be defined as the difference in monetized outcome measures (that is, absenteeism and presenteeism costs) between 100-h and 40-h VR during the measurement period (that is, intervention period and follow-up, see Fig. 2), with positive benefits indicating reduced spending in the 40-h group. To estimate uncertainty, 95 % CIs around the benefit estimates and NB will be estimated by means of bootstrap confidence intervals. Financial returns of 40-h VR are positive if the following criteria are met: NB > 0, BCR > 1, and ROI > 0 % [25].

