### Context of this study

In the Netherlands, both employer and employee are responsible for the work participation process of the sick-listed employee during the first 2 years of sick leave. The employer and employee can be supported by a certified reintegration company and/or an occupational physician (OP). In the first 2 years of sickness, the employer is responsible for the costs of wage replacement, which is regulated by the Dutch Gatekeeper Improvement Act [64]. As a result of this act, the employer has to reimburse the work participation coordination module (costs: approximately €1,200) for both interventions performed in this study. The other intervention modules are reimbursed by healthcare insurers.

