## Appendix 1: Intervention modules

### Work participation coordination

Work participation coordination is carried out by a work participation coordinator [71] and encompasses a workplace visit, case management, and two evaluation moments. The workplace visit includes an ergonomic workplace analysis and a consultation with employer and employee (patient), with the aim of developing a work participation plan. Case management consists of individual coaching sessions with the patient and unplanned ad hoc conversations with the patient during the program. The coaching style of the work participation coordinator is mainly based on solution-focused coaching [72, 73] and on empowerment [74]. The two evaluation moments include a report on progression in work participation, which will be performed at mid-term and discharge.

Dosage: 10 hours in both programs.

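### The employer benefit-cost ratio and return on investment do not fit a comparison in which the employer pays the same intervention cost in both arms

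*Protocol article*

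**What the plan says.** The section on the employer's perspective (Protocol article, Cost-benefit analysis) restricts the analysis as follows: "only the costs relevant to the employer will be considered, including intervention, absenteeism, and presenteeism costs". It names three metrics: net benefits (benefits minus costs), the benefit-cost ratio ("BCR = benefits/costs") and return on investment (benefits minus costs, divided by costs, as a percentage).

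The two terms are then defined. For benefits: "Benefits will be defined as the difference in monetized outcome measures (that is, absenteeism and presenteeism costs) between 100-h and 40-h VR". For costs: "Costs will be defined as intervention costs". The decision rule follows: "Financial returns of 40-h VR are positive if the following criteria are met", the criteria being NB > 0, BCR > 1 and ROI > 0 %. Bootstrap 95 % intervals are planned for the benefits and for NB.

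Two other places settle what the employer pays. Context of this study says that "the employer has to reimburse the work participation coordination module", at roughly €1,200, for both interventions, and that health insurers pay for the remaining modules. Appendix 1 sets the amount of that module: "Dosage: 10 hours in both programs".

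**The concern.** The benefit term is a difference between arms. The cost term is not stated as a difference, and the employer's part of the intervention cost is the same in both arms by design. A ratio of an incremental benefit to a cost makes sense only if the cost is incremental too, and here that increment is about zero.

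At stake is the employer conclusion. The Discussion counts the two-perspective economic evaluation among the study's strengths, stresses informing employers about return on investment, and expects employers to gain a higher return if the hypothesis is valid. With the printed rule, two of the three metrics either cannot be computed or answer a different question from the one the employer faces in choosing between the two programmes. If the choice between full and incremental cost stays open until the data are seen, it can also change the reported employer result.

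**Working it through.** The protocol gives no value for NB, BCR or ROI, so there is no figure to reproduce. The check puts the stated inputs into the printed formulas.

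**Inputs**
- Employer-paid intervention cost: about €1,200 per worker in each arm (Context of this study; the same 10 hours in both arms, Appendix 1).
- B: absenteeism plus presenteeism costs, 100-h minus 40-h, per worker. The protocol gives no value, so a range from −€600 to €2,000 is assumed for illustration.
- NB = B − C; BCR = B/C; ROI = (B − C)/C × 100.

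**When the three criteria agree.** For C > 0, B − C > 0, B/C > 1 and (B − C)/C > 0 are the same condition. For C = 0 only the first is defined.

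**Incremental cost.** C = 1,200 − 1,200 = €0. Then NB = B − 0 = B for every B. BCR = B/0 and ROI = (B − 0)/0 are undefined, so a rule that requires all three cannot be applied, whatever the data show.

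**Full cost of the 40-h arm.** C = €1,200:

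| B (€) | NB = B − 1,200 (€) | BCR = B/1,200 | ROI (%) | Label under the rule | NB with C = 0 (€) |
|---|---|---|---|---|---|
| −600 | −1,800 | −0.50 | −150 | not positive | −600 |
| 0 | −1,200 | 0 | −100 | not positive | 0 |
| 600 | −600 | 0.50 | −50 | not positive | 600 |
| 1,200 | 0 | 1.00 | 0 | not positive | 1,200 |
| 2,000 | 800 | 1.67 | 66.7 | positive | 2,000 |

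Every NB is €1,200 lower than the employer's actual consequence of choosing 40-h over 100-h, because a cost paid under either programme is charged to one of them. Savings above €0 and up to €1,200 are therefore given the wrong label.

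**Small observed cost differences.** The 40-h programme may be extended, which the protocol intends in no more than 5 % of cases. Assume that those workers incur 10 % to 50 % extra module cost (the protocol gives no figure):
- 0.05 × 0.10 × 1,200 = €6
- 0.05 × 0.50 × 1,200 = €30

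With B = €600:
- NB = 600 − 6 = €594 and 600 − 30 = €570
- BCR = 600/6 = 100 and 600/30 = 20

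NB hardly moves, while BCR changes fivefold through a denominator close to zero. A small non-zero difference makes the ratios computable but not interpretable.

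**The case against.** Several points on the other side have force.

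- **NB survives.** Under the incremental reading NB is defined and is the right employer quantity, and its bootstrap interval is already in the plan. The fault does not void the employer analysis. This stands.
- **The full-cost rule is coherent in itself.** With C = €1,200 the three criteria always agree. What is wrong is the mismatch between a full cost and an incremental benefit, which sets too high a threshold. This also stands.
- **The article is condensed.** Whether costs are full or incremental may be specified in a document not shown, and the source cited for the method is not available. That would excuse an omission, but it does not rescue the printed rule: either specification leads to one of the two failures above.
- **Reach.** The societal ICER is explicitly a ratio of differences in cost and effect, and neither it, the cost-utility analysis nor the primary non-inferiority test uses these formulas. This stands and limits the severity.

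Three stronger readings are tempting, and the documents do not support them.

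- A reader might take intervention costs to mean all programme costs whoever pays, expect a negative increment because 40-h has about 60 fewer hours (100 − 40), and conclude that the three criteria contradict each other. The section limits costs to those relevant to the employer, and the insurers pay for the other modules, so the text excludes this reading. The documents also give no cost for those modules.
- A reader might infer that the plan will report a loss for 40-h. That follows only under the full-cost reading, which the protocol never states.
- A reader might defend the full cost as a return on each programme separately. That needs benefits measured against having no programme, and the trial has no such arm.

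**Conclusion.** The point holds for BCR and ROI and for the three-part rule, not for NB. Neither reading that the text permits yields a valid test of NB > 0, BCR > 1 and ROI > 0 % for 40-h versus 100-h. With incremental costs, two of the three criteria are undefined, or unstable if small cost differences arise. With the full cost, the break-even point moves from €0 to €1,200 per worker, against 40-h.

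This rests on the employer paying only the coordination module and on its cost being the same in both arms. Both are stated in the protocol, though the €1,200 is approximate. The values of B and the extra cost of an extension are illustrative assumptions, and the conclusion does not depend on them.

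Should-fix: the fault is confined to the secondary employer analysis and is cheap to correct.

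**What to change.** In the analysis plan, define the cost term as the mean employer-paid intervention cost in the 40-h arm minus that in the 100-h arm, which is about zero by design. Then NB is the benefit (100-h minus 40-h absenteeism and presenteeism costs) minus that cost difference. Judge the employer result by NB > 0, reported with the bootstrap 95 % interval already planned. Drop BCR and ROI, and their two criteria, for the 40-h versus 100-h contrast.

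This is a change of wording and needs no new data. The price is that two planned ratios are no longer reported. The employer perspective itself is kept.
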